### 9.2. Analysis Populations

#### Safety Population (Safety)

The Safety population will consist of all randomised patients who have received any amount of study medication. Patients will be analysed as treated.

#### Intent-To-Treat Population (ITT)

The Intent-to-Treat (ITT) population will consist of all randomised patients who have received any amount of study medication. Patients will be analysed as randomized.

#### Efficacy Evaluable (EE) Population

The efficacy evaluable (EE) population will include those patients in the ITT population meeting pre-defined criteria as follows:

1. Having completed a full course of study medication and having known efficacy endpoints.
2. No missed dose due to vomiting, as recorded on the 'study medication administration page' of the CRF, except at Day 0 where a patient may vomit after the first drug administration and have a repeat full dose. In this case, the repeated dose should not be vomited.

3. No concomitant medication (except paracetamol) which may interfere with the treatment outcome, up to Day 14. The list of forbidden medication is given in Attachment 5. A medical review will be performed to confirm the exclusion of a patient from the EE population.
  4. No concomitant disease, such as Tuberculosis, HIV, severe URTI, gastrointestinal disease, etc..., which may interfere with the clear classification of the treatment outcome. A medical review of the experienced diseases will be performed to define the list of patients excluded from the EE population.
  5. No major protocol violation. The list of all protocol violations will be assessed with regards to their impact (major/minor) prior to database lock.
- The list of patients excluded from the EE population will be reviewed and approved prior to study unblinding and database lock.

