| Concomitant Treatment      | 
The administration of paracetamol/acetaminophen (<math>\leq 1</math> g) on Day 0, 1 and 2 is allowed if the patient's condition warrants it and should be recorded in the appropriate section of the CRF.
 
Rescue treatment: Treatment failures will be treated with best antimalarial therapy available in the country where the study is conducted.
 
If during follow-up, infections other than malaria require the administration of drugs with antimalarial activity (such as co-trimoxazole, tetracycline or doxycycline), the patient will be considered a protocol violator, with the exception of patients given tetracycline as eye ointment.
 
All concomitant medications taken by the patient during the study, from the date of signature of the informed consent will be recorded in the appropriate section of the CRF.
                                                                                                                                                            |
| Study Drugs Administration | 
Study drug will be administered orally once a day for three consecutive days, i.e. on Days 0, 1 and 2, by authorized member of the investigation team.
 
Depending on their body weight, patients will receive a total of between 2 to a maximum of 8 tablets per day on Days 0 and 1 and a total of between 1.5 to a maximum of 6 tablets per day on Day 2.
                                                                                                                                                                                                                                                                                                                                                                                                                                                                                                                                                                                                                                                  |

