#### Primary Efficacy Endpoint

The primary efficacy endpoint for the study is the cure rate on Day 14.

Cure on Day 14 will be defined as no parasitemia on Day 14 irrespective of axillary temperature without previously meeting any of the criteria of treatment failure throughout the follow-up period.

Treatment failure is defined as any of the following:

- ◆ Clinical deterioration due to *P. vivax* illness requiring hospitalization in presence of parasitemia.
- ◆ Presence of parasitemia and axillary temperature  $\geq 37.5^{\circ}\text{C}$  any time between Day 3 and Day 28.
- ◆ Presence of parasitemia on any day between Day 7 and Day 28 irrespective of clinical condition.

Patients presenting a *P. falciparum* infection after clearance of *P. vivax* parasites should be treated accordingly and withdrawn. They should not be considered as *P. vivax* treatment failures.

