#### Secondary Efficacy Endpoints

The secondary efficacy endpoints are:

- Cure rate on Day 21 and Day 28, defined in the same way as cure rate on Day 14.
- Parasite Clearance Time (PCT).

Parasite clearance time is defined as the time from first dosing to time of first blood draw with parasite clearance. Parasite clearance

is defined as zero presence of asexual parasites for two consecutive negative readings taken between eight and twenty-four hours apart.

➤ **Fever Clearance Time (FCT)**

Fever clearance time is defined as the time from first dosing to first normal reading of temperature ( $<37.5^{\circ}\text{C}$  taken axillary or tympanic) for two consecutive normal temperature readings taken between eight and twenty-four hours apart.

The method of temperature measurement must be the same (i.e. axillary, tympanic, oral or rectal) for all measures in the same patient. Those patients who are initially included on history of fever and who do not subsequently have a documented temperature reading of over  $37.5^{\circ}\text{C}$  (taken axillary or tympanic) during the 24 hours following initial dosing, will not be included in this endpoint analysis.

- Proportion of patients who have cleared parasites on Day 1, 2 and 3
- Proportion of patients who have cleared fever on Day 1, 2 and 3

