#### **Secondary Efficacy Analyses:**

The primary efficacy analysis performed on Day 14 will be repeated for the proportion of patients with cure on Day 21 and 28, using the efficacy evaluable population.

In addition, the analysis performed using the EE population will be repeated using the ITT population.

The parasite clearance time and fever clearance time will be analysed using Kaplan-Meier estimates. The median and quartiles clearance time will be presented together with the corresponding 95% confidence intervals. The mean will also be calculated. The survival curves will be presented. The log rank test will be used to compare the parasite clearance time and fever clearance time between the two treatment groups. Patients who do not have documented parasite or fever clearance will be censored. Censoring time will be greater than the highest observed clearance time.

The proportion of patients who have parasite clearance and the proportion of patients who have fever clearance will be presented at Day 1, Day 2 and Day 3. The associated exact 95% confidence interval will also be calculated.

The number of parasites will be summarized using standard descriptive statistics, as well as geometric mean and its associated 95% confidence interval using an analysis of variance model on  $\log_{10}$  transformed parasites counts with treatment and site as factors. The mean parasite count at each scheduled timepoint will be presented graphically.

All secondary efficacy analyses will be performed both on the EE and ITT populations.

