**Exploratory Analyses:**

The primary efficacy analysis performed on Day 14 will be repeated for the proportion of patients with PCR-corrected cure on Day 14 and 28, using the efficacy evaluable population and the ITT population.

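### The efficacy-evaluable rule on interfering medication stops at Day 14, yet the same population is used for Day 21, Day 28 and PCR-corrected Day 28 cure (minor)

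*Protocol*

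**What the plan says.** Protocol section 9.2 sets out one EE population with five criteria. Criterion 3 requires "No concomitant medication (except paracetamol) which may interfere with the treatment outcome, up to Day 14", with the drugs listed in Attachment 5 and a medical review to confirm exclusions. Criterion 4 (interfering concomitant disease) and criterion 5 (major protocol violation) carry no day limit. Criterion 1 asks for known efficacy endpoints without naming a day.

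Section 9.5.2 assigns this population to later endpoints. Under Secondary Efficacy Analyses, the Day 14 analysis is to be "repeated for the proportion of patients with cure on Day 21 and 28, using the efficacy evaluable population". Under Exploratory Analyses, it is to be "repeated for the proportion of patients with PCR-corrected cure on Day 14 and 28, using the efficacy evaluable population", and also on the ITT population.

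Section 9.5.1 defines cure by the slide and the absence of earlier failure: "no parasitemia on Day 14 irrespective of axillary temperature without previously meeting any of the criteria of treatment failure". The later endpoints follow suit: "Cure rate on Day 21 and Day 28, defined in the same way as cure rate on Day 14". Neither definition has a rule for interfering drugs.

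Elsewhere the prohibition is not limited to Day 14. Attachment 5 bars the listed drugs from 14 days before enrolment to the end of the study. Section 3.3 classes antimalarial use other than for treatment failure as a protocol violation. The Synopsis (Concomitant Treatment) says that if another infection during follow-up requires a drug with antimalarial activity, "the patient will be considered a protocol violator, with the exception of patients given tetracycline as eye ointment".

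**The concern.** The Day 14 limit fits the primary endpoint but not the two later ones analysed in the same set. A patient treated for another infection on Day 20 with a listed antibiotic satisfies criterion 3. If parasites have not already reappeared, a negative Day 28 slide counts as cure, although an active drug other than the study treatment may have produced it. Such masking shrinks any true difference between arms, which in a non-inferiority comparison favours the test treatment.

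The ITT repeat does not correct this, because it uses the same cure definition and also has no rule for interfering drugs.

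If reviewers instead remove the patient under criterion 4 or 5, there is only one EE set to remove the patient from. The Day 14 result, complete before the drug was taken, would go as well.

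**Working it through.** **Plan's own figure.** Inputs from section 9.4: 90% cure in both arms, margin 10 points, two-sided 95% interval, 90% power, 205 evaluable patients per arm, 10% dropout, 456 randomised. The Farrington-Manning formula is n = (z₀.₉₇₅·s₀ + z₀.₉₀·s₁)² / 0.10². The restricted null proportions are 0.8313 and 0.9313.

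- s₀² = 0.8313×0.1687 + 0.9313×0.0687 = 0.2042, so s₀ = 0.4519.
- s₁² = 2×0.9×0.1 = 0.18, so s₁ = 0.4243.
- n = (1.960×0.4519 + 1.2816×0.4243)² / 0.01 = 204.3, i.e. 205 per arm.
- 410 / 0.90 = 455.6, i.e. 456.

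The stated figures are reproduced. They concern Day 14 only, so this point does not change them.

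**What happens to a patient who takes a listed drug on Days 15-28, has not already failed and has a negative later slide**

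| Route | Day 14 primary (EE) | Day 21/28 cure (EE) |
|---|---|---|
| Passes criterion 3; not removed under 4 or 5 | Kept, valid | Counted as cure |
| Removed under criterion 4 or 5 | Valid outcome dropped | Dropped |

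Neither route gives the natural result, which is to keep the patient at Day 14 and exclude the patient from EE at the later endpoint. Patients given rescue treatment after failure are not affected, because they already count as failures.

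**Size if the patient is kept.** Let f be the share of patients exposed on Days 15-28. The Protocol gives no value, so f is assumed at 2%, 5% and, as an outer case, 10%, equal in both arms. If the drug masks every failure among users, an arm with true cure p shows p + f(1−p), and the observed difference is (1−f) times the true one. With assumed true Day 28 cure of 90% (chloroquine) and 80% (test), and 205 per arm:

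| f | Observed chloroquine | Observed test | Difference (points) | Exact chance of declaring non-inferiority |
|---|---|---|---|---|
| 0 | 90.0% | 80.0% | −10.0 | 2.6% |
| 2% | 90.2% | 80.4% | −9.8 | 3.0% |
| 5% | 90.5% | 81.0% | −9.5 | 3.7% |
| 10% | 91.0% | 82.0% | −9.0 | 5.1% |

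**Size if the patient is removed.** With 205(1−f) per arm at Day 14, Farrington-Manning power is Φ[(0.10·√n − 1.960·s₀)/s₁]:

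| f | n per arm | Power |
|---|---|---|
| 0 | 205 | 90.1% |
| 2% | about 201 | 89.5% |
| 5% | about 195 | 88.5% |
| 10% | about 185 | 86.7% |

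**The case against.** The strongest reply is that the Protocol has other filters and that the remaining detail belongs to the statistical analysis plan, which sections 9 and 9.5.2 promise before database lock and which is not shown. Part of this stands. Criterion 4 has no day limit, and an infection that calls for one of these drugs might itself exclude the patient after medical review; criterion 5 might do so too. So passing criterion 3 does not by itself make the patient a counted cure. But both criteria act on the one EE set and do not supply a rule by endpoint. The Day 14 limit, and the use of that set at Days 21 and 28, are fixed in the Protocol itself.

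A reader might infer that such patients will be lost from the Day 14 primary analysis. The text does not support that as a consequence. The Synopsis and section 3.3 call the patient a violator, not a major one. Criterion 5 grades violations by impact, and a drug taken on Day 20 cannot affect a Day 14 slide. The exclusion list is also approved before unblinding. Loss from the primary is a possibility that the wording leaves open.

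A reader might also take criterion 1 to require a known Day 28 result before a patient enters the primary. It can equally mean the endpoint being analysed, and section 9.1 reports observed data without imputation, so this is not a contradiction.

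Finally, a reader might equate the share exposed with the bias. If 3-5% were exposed, that many slides would be confounded, but only the would-be failures among those patients move the cure rate. With an assumed failure rate of 10-20%, the shift is at most 0.03×0.10 to 0.05×0.20, about 0.3 to 1.0 points per arm.

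**Conclusion.** The mismatch is real and lies in the text: a Day 14 medication limit governs a population used at Days 21 and 28, in a protocol that forbids the same drugs throughout. Its effect is small. At an assumed 2-5% exposure, a true −10 points appears as −9.8 to −9.5, and the chance of a false non-inferiority finding at Day 28 rises from 2.6% to between 3.0% and 3.7%. These figures rest on equal exposure in both arms, masking of every failure among users, and true Day 28 cure of 90% versus 80%; none of these comes from the Protocol, and complete masking is the worst case. The bias falls on secondary and exploratory endpoints. The Day 14 conclusion is touched only if reviewers exclude patients for events after Day 14, and the cost is then about 0.6 to 1.6 points of power at 2-5% exposure. The 205 per arm and 456 randomised stand. Severity: minor.

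**What to change.** In section 9.2, replace the fixed Day 14 limit in criterion 3 with a limit at the day of the endpoint being analysed. Define EE separately for Days 14, 21 and 28, and apply criteria 1, 3, 4 and 5 only to events up to that day. In section 9.5.2, use EE-14 for the primary and for PCR-corrected Day 14 cure, EE-21 for Day 21 cure, and EE-28 for Day 28 and PCR-corrected Day 28 cure. State as well how an interfering drug taken before the endpoint is handled in the ITT analysis, since changing EE does not settle that.

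The cost is a few words, two extra population flags and a slightly smaller EE-28 denominator. The sample size and the Day 14 analysis plan do not change.

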### **3.3. Patient Discontinuation or Protocol Violation**

A patient may withdraw consent at any time, without prejudice for further follow up or treatment by the study site.

A patient may be discontinued prematurely from the study if the Investigator decides that a patient should be withdrawn for safety reasons, due to an adverse event of such a nature or intensity (including abnormal laboratory finding), where study drug withdrawal or withdrawal from the study is advisable. Information concerning any adverse event and symptomatic treatment given must be recorded on the case record form (CRF). If the adverse event is serious, the Investigator must notify the Sponsor or its designee immediately and the reporting procedures described in the safety section must be followed. Definitions and reporting requirements for adverse events are provided in section 5.2.4.

Self or third party administration of antimalarial (or antibiotics with antimalarial activity) treatment other than for treatment failure will be classified as a protocol violation. A list of Forbidden Medication is provided in Attachment 5.

In the case of a patient vomiting the first dose (Day 0) within 0 to 30 minutes of study drug administration, a repeat full dose will be given. If patient vomits the study drug on either the second (Day1) or third day (Day 2) of dosing or if the patient vomits a re-administered dose on Day 0, they will not be re-dosed but will be withdrawn from the study. A patient who is withdrawn due to vomiting should receive rescue medication, after having completed end of study (Day 28) assessments.

A patient who terminates participation after any study drug administration for any reason will be considered as having discontinued from the study and will have

end of study (Day 28) procedures performed. The reason for discontinuation will be recorded on the CRF. If a patient is discontinued for an adverse event, the Investigator will continue to follow the patient until resolution or until no further medically relevant information can be expected.

Every effort must be made to schedule a follow-up visit for patients who fail to return to the study site after administration of the study drug. Women who inadvertently become pregnant during the study must be followed to full term and the outcome of the birth fully documented on a specific form provided by Sponsor.

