#### **4.11. Rescue Medication**

Treatment failures will be treated with the best antimalarial therapy available in the country where the study is conducted. All procedures to be performed at Day 28, including sampling for PCR, preparation of a thin and thick films and **whole blood sample for measurement of pyronaridine and/or chloroquine/chloroquine metabolites blood levels** must be undertaken before rescue medication is administered.

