|                                            | 
 
➤ Blood biochemistry and urinalysis
 
➤ Thick blood films (2) prepared 8-hourly
 
➤ Adverse events recording
 
➤ Concomitant medication recording
 
➤ Patient scheduled for follow up visits on Days 7, 14, 21, 28, 35 and 42
 
➤ Patient may be discharged from study site if parasite- and fever-free, with instructions to return in case of any recurrence of symptoms
 
 
note: If parasites and fever have not cleared on Day 3, the patient should be followed up until total clearance of parasites. If parasitaemia remains significant, the patient should be viewed as a treatment failure and withdrawn from the study. All End of Study Assessments (Day 28) should be performed before discharge and before rescue medication is given.
 
 
➤ Patient provided with an appropriate bed net
 
 |
| Assessment D7
(+/- 1 day)       | 
 
➤ Vital signs: BP and HR
 
➤ Temperature recorded
 
➤ Clinical signs and symptoms of malaria (if clinically indicated)
 
➤ 12-lead ECG (if clinically indicated)
 
➤ Haematology
 
➤ Blood biochemistry and urinalysis
 
➤ Thick blood films (2) for asexual parasites and gametocytes counts (the total count is recorded)
 
➤ Thin blood film (as a reserve)
 
➤ Sample for PCR (as a reserve)
 
➤ Adverse events recording
 
➤ Concomitant medication recording
 
                                                                                                                                                                                                                                                                                                                                                     |

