### **9.4. Determination of Sample Size**

Assuming a cure rate on Day 14 of 90% in both treatment groups and assuming a non-inferiority limit of -10%, then a sample size of 410 evaluable patients randomized in 1:1 ratio (205 patients in each treatment group) would provide 90% power to demonstrate non-inferiority of PA compared to the chloroquine, using a two-sided 95% confidence interval with Normal approximation. Assuming a drop out rate of 10%, 456 subjects would be randomized to the study (228 subjects in each treatment group).

Assuming a cure rate on Day 14 of 95%, this sample size would provide >99% power to demonstrate non-inferiority of PA compared to the chloroquine.

Sample size estimation was performed using nQuery statistical software version 4.0.

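### The efficacy evaluable rules for the sole primary analysis drop treatment failures that occur before the third dose, and can be read to drop failures rescued by Day 14 as well

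*Protocol*

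**What the plan says.** Section 9.5.2 of the protocol places the primary Day 14 non-inferiority test on the EE population. The ITT repeat is listed among the secondary analyses.

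Section 9.2 sets the EE criteria. Criterion 1 is "Having completed a full course of study medication and having known efficacy endpoints". Criterion 3 is "No concomitant medication (except paracetamol) which may interfere with the treatment outcome, up to Day 14", with a reference to Attachment 5 and a medical review to confirm each exclusion. Attachment 5 lists antimalarials barred throughout the study. It makes an exception for chloroquine and primaquine used as study material, but none for rescue.

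Section 4.11 says "Treatment failures will be treated with the best antimalarial therapy available in the country where the study is conducted". Under 9.5.1, clinical deterioration with parasitaemia that requires hospitalisation is a failure with no day attached, parasitaemia with fever is a failure from Day 3, and parasitaemia alone is a failure from Day 7. The Section 6 schedule puts rescue on the day of failure.

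Two other passages bear on the point. Section 3.3 says that antimalarial "treatment other than for treatment failure will be classified as a protocol violation". The Day 3 note in Section 6 says "If parasitaemia remains significant, the patient should be viewed as a treatment failure and withdrawn from the study".

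For the later endpoints, the primary analysis "will be repeated for the proportion of patients with cure on Day 21 and 28, using the efficacy evaluable population".

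**The concern.** A treatment failure is the event that the primary endpoint counts. If a population rule removes patients because they failed, or because of what was done after they failed, they leave both numerator and denominator. The arm with more failures loses more patients, both cure rates rise, and the difference moves toward zero. In a non-inferiority test this favours the new drug, and a treatment at or beyond the margin can pass.

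Criterion 1 does this for a narrow group. A patient who is hospitalised with deterioration before the third dose and switched to rescue has failed, but has not completed the course. Criterion 3 could do it for a much larger group, because a failure found at Day 7 or Day 14 receives an antimalarial inside its window. Section 9.2 contains no sentence that keeps either group in EE.

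**Working it through.** **Inputs from section 9.4.** 90% cure in both arms, 205 evaluable per arm, 90% power, 10% drop-out, "assuming a non-inferiority limit of -10" percent, "using a two-sided 95% confidence interval with Normal approximation" (one-sided 2.5%).

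**The plan's own figure.**
- Unpooled normal formula: 2 × 0.9 × 0.1 × (1.960 + 1.282)² / 0.10² = 189.1, so 190 per arm.
- Farrington-Manning, with the variance restricted under the null (rates 0.931 and 0.831): [(1.960 × 0.452 + 1.282 × 0.424) / 0.10]² = 204.3, so 205 per arm. This matches.
- Randomised total: 410 / 0.9 = 455.6, so 456. This matches.
- Power at 95% cure: 99.6%, in line with the stated figure above 99%.

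The sample size is not in question. It also shows what the authors expected: 10% of 410 is about 41 failures inside the evaluable set.

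**Effect of excluding failures.** Let p be the true cure rate and f the share of Day 14 failures excluded from EE. The documents do not give f; it is an assumption, as is its being equal in both arms.
- EE cure rate = p / (1 − f(1 − p))
- EE patients per arm = 205 × (1 − f(1 − p))
- P(non-inferiority) = Φ((d + 0.10)/SE − 1.96), where d is the EE difference and SE its unpooled standard error

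Take the truth at the margin: 90% on chloroquine, 80% on pyronaridine artesunate (PA).

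Worked case, f = 10%:
- Chloroquine: 0.9/0.99 = 0.9091, n = 203.0
- PA: 0.8/0.98 = 0.8163, n = 200.9
- d = −0.0928
- SE = √(0.0826/203.0 + 0.1499/200.9) = 0.0340
- (0.0072/0.0340) − 1.96 = −1.75, so P = 4.0%

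| Excluded share f | EE chloroquine | EE PA | Difference (points) | P(NI), normal | P(NI), exact |
|---|---|---|---|---|---|
| 0 | 90.0% | 80.0% | −10.0 | 2.5% | 2.6% |
| 5% | 90.5% | 80.8% | −9.6 | 3.2% | – |
| 10% | 90.9% | 81.6% | −9.3 | 4.0% | – |
| 25% | 92.3% | 84.2% | −8.1 | 8.5% | 9.4% |
| 50% | 94.7% | 88.9% | −5.8 | 31% | 33.5% |
| 75% | 97.3% | 94.1% | −3.2 | 89% | 86.6% |

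The exact column enumerates both binomials and applies the 95% Wald lower limit, with EE numbers rounded to whole patients. At a true 90% against 75%, beyond the margin, the exact probability rises from 0.05% at f = 0 to 5.9% at f = 50%.

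**Which rows belong to which criterion.** Before Day 3 only the deterioration criterion can be met, so criterion 1 alone belongs near the small-f rows. The 25% to 75% rows apply only if criterion 3 is read literally.

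**The case against.** A reader might infer that every rescued failure drops out of EE. The documents do not establish that, and several passages point the other way.

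- Criterion 3 covers only medication that may interfere with the outcome. Cure requires no earlier failure, so rescue given after failure cannot change the classification. Each exclusion also needs medical review, and a reviewer asked to confirm can decline.
- Section 3.3 exempts antimalarials given for treatment failure from being a protocol violation, so criterion 5 does not remove these patients. Rescue also has its own section (4.11), separate from concomitant and forbidden medication (4.10).
- A documented failure can be read as a known efficacy endpoint.
- The sample size assumes 90% cure among evaluable patients. Under the literal reading most Day 14 failures would leave, and EE cure would approach 100% in both arms.
- The ITT repeat includes every dosed patient, and the list of EE exclusions is approved before unblinding.

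These arguments make the literal reading of criterion 3 doubtful, but they do not close the gap. The 3.3 exemption is about violations and is not carried into criteria 1 or 3. The stated task of the medical review is to confirm exclusion, and no rule tells it to keep failures. In criterion 1 the known endpoint is required in addition to the full course, so it cannot rescue a patient who stopped early. The ITT result does not enter the non-inferiority decision. Nor is this a detail left to the analysis plan, because the protocol itself fixes the criteria.

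A reader might also infer that the Day 3 patient in Section 6 meets none of the listed failure criteria. That is not shown. The note opens with parasites and fever both uncleared, and such a patient may meet the parasitaemia-with-fever criterion. What stands is that its failure sentence asks only for significant parasitaemia, an undefined term absent from 9.5.1 and Attachment 3.

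**Conclusion.** The point holds in two parts of different strength. Criterion 1, as written, removes failures that occur before the third dose. The protocol describes vital organ dysfunction in this disease as very rare, so the group is probably small: at an assumed 5% to 10% of failures, the error rate goes from 2.5% to about 3% to 4%. Criterion 3 is ambiguous. If applied literally, the error rate could reach about 9% with a quarter of failures excluded and 31 to 34% with half. The protocol does not say that this will happen, and part of its text argues against it.

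The direction of the bias is certain whenever the worse arm has more failures and the same share is excluded from each. Its size is not known: all the probabilities rest on an assumed share f, on true rates placed at or beyond the margin, and on 205 evaluable per arm before the exclusion. Because the wording decides whether the sole primary test keeps its 2.5% error, it should be settled before unblinding.

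Reusing EE for Days 21 and 28 with a medication window that ends at Day 14 is a minor, secondary point. The synopsis makes later use of drugs with antimalarial activity for other infections a violation, so criterion 5 may cover it.

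**What to change.** - **Section 9.2:** state that a patient who meets a treatment-failure criterion on or before the analysis day stays in EE as not cured. State that criteria 1 and 3 apply only up to the time of failure, so that rescue given after failure is not a reason for exclusion.
- **Section 6, 9.5.1 and Attachment 3:** reconcile the Day 3 note with the three listed failure criteria, so that a patient withdrawn as a failure is classified the same way in the analysis. Which clinical rule applies is for the sponsor to decide.
- **Minor:** tie the criterion 3 window to the day being analysed (14, 21 or 28).

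This is a change of wording before unblinding and database lock, with no new data. The sample size stays at 410 evaluable and 456 randomised. If criterion 3 would otherwise have been applied literally, observed EE cure rates will be somewhat lower.
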